### Statistical analysis

Statistical analyses will include “intention-to-treat”-evaluation for all cohorts’ primary and secondary endpoints and “per-protocol”-evaluation for explorative endpoints. “Per protocol” is defined as administration of RT- and 5-ALA-applications according to prescribed dose. Descriptive measures for all variables will be given. Rates of adverse events will include all events qualifying for CTCAE grade 3 or greater and the final DLT-rate will be estimated by use of the Bayesian Time-to-Event Continual Reassessment Method (Tite-CRM). Survival parameters will be analyzed using the Kaplan-Meier method and two-sided log-rank tests for comparative analyses between defined subgroups. Cox regression testing will estimate impact of risk factors (e.g. age, KPS, gender) on these parameters.

All data will be compared to historical data using the Mann-Whitney U test, Fisher’s exact test, or Chi² test.

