## Methods

### Trial design, setting and recruitment

This is a prospective, single-armed, single center phase I/II dose escalation-study, based in the University Hospital of Münster, Germany. The aim of the study is to determine the maximum tolerated dose (MTD) and safety of repeated application of oral 5-ALA as a radiosensitizer during (neo)adjuvant radiotherapy for the treatment of glioblastoma recurrence. All patients will receive 36 Gy adjuvant RT in 20 fractions. An increasing number of RT-fractions will be conducted as radiodynamic therapy (RDT), which will consist of 1.8 Gy-irradiation 7–9 h after oral application of 20 mg/kg bodyweight 5-ALA in a tap-water-solution.

Recruitment will start in cohort 0 with one RDT-fraction and patients will be allocated consecutively to this and the following cohorts, which will be numbered sequentially from 0 to 8. Each cohort encompasses three initial patients being expanded by additional three participants in case of a dose limiting toxicity (DLT), following a 3 + 3-design. With increasing cohort number, the quantity of RDT-fractions will be increased by one with a maximum of eight adjuvant applications in cohort 8. Additionally, in cohorts 0 and 1, patients will receive two neoadjuvant RT-fractions (in case of cohort 1, the first fraction will be conducted as RDT). In these cohorts, a decisive histopathological analysis of the resected tissue will account for changes induced by neoadjuvant therapy. MDT is considered to be reached in case of DLT in two or more patients on the same dose level. A study continuation with the next dose-level will be evaluated and approved by the data safety and monitoring board (DSMB) after a six-week follow-up of the last RT-fraction of the last patient within a cohort. The study started recruitment with the first patient in Q1 2023 with an estimated study duration of 30 months.

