### Study population

26 patients will be recruited with additional 15–20% drop-outs, cumulating in approximately 30 patients. End of study is defined as the last patient’s last visit (six-month follow-up). For each drop-out, a new patient will be entered into the study at the same dose level.

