#### Blood and tissue samples

Tissue sampling and evaluation of morphological changes in brain tissue will be performed on cohorts 0 and 1 after neoadjuvant treatment. These analyses will therefore include tissue changes after sole RT (cohort 0) as well as RDT (cohort 1), based on parameters like Caspase-3, IBA1, H&E, EvG, P53, Ki67 and gammaH2AX. Blood samples will be drawn for safety clearance as part of toxicity assessment and to monitor changes of ALA-metabolites in serum (PPIX) before every application of 5-ALA. Additional blood samples for analysis of concentration changes in radiobiological markers (including markers like IL-6, IL-8, TNF-Alpha and VEGF) will be drawn during neoadjuvant treatment (day − 3 and day − 2) and at the beginning (day 1 and day 2) and end (day 20) of adjuvant treatment.

Concentration changes of 5-ALA-metabolites in urine samples will be evaluated during neoadjuvant treatment (day − 3) and surgery (day 0) for cohorts 0 and 1 and at the beginning (day 1) and first follow-up for all study participants.

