### End-points

Primary: To determine the maximum tolerated dose and safety of (neo)adjuvant RDT. MTD is defined as maximum dose level before two or more patients suffer from DLT.

Secondary: To evaluate six-months overall survival rate (OSR), six-months progression-free survival rate (PFSR) and six-months event-free survival rate (EFSR), as well as histological tissue changes after neoadjuvant treatment. OSR, PFSR and EFSR will be determined from study inclusion to the second follow-up, six months after the beginning of adjuvant treatment.

Exploratory: To explore concentration changes of 5-ALA metabolites in urine samples and changes of radiobiological marker concentration in blood serum samples.

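### The MTD and DLT rate are assigned to intention to treat, so a patient who misses RDT fractions without a DLT and is not replaced counts as DLT-free at a level not received

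*Protocol article*

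**What the plan says.** Four statements in the protocol article bear on this point.

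- **Analysis set (Statistical analysis).** "Statistical analyses will include “intention-to-treat”-evaluation for all cohorts’ primary and secondary endpoints". Exploratory endpoints get the other set: "Per protocol” is defined as administration of RT- and 5-ALA-applications according to prescribed dose". The article thus separates patients dosed as prescribed from all patients, and puts the primary endpoint with the latter.
- **What a level is (Trial design, setting and recruitment).** The 5-ALA dose per administration is constant and the number of administrations rises: "the quantity of RDT-fractions will be increased by one with a maximum of eight adjuvant applications in cohort 8".
- **Decision rule (same section and End-points).** "Each cohort encompasses three initial patients being expanded by additional three participants in case of a dose limiting toxicity (DLT), following a 3 + 3-design", and "MTD is defined as maximum dose level before two or more patients suffer from DLT". This is a count of patients with a DLT. Statistical analysis adds a final DLT rate estimated by TITE-CRM.
- **Drop-outs (Study population).** "26 patients will be recruited with additional 15–20% drop-outs, cumulating in approximately 30 patients", and "For each drop-out, a new patient will be entered into the study at the same dose level". The article does not say what makes a patient a drop-out.

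**The concern.** Intention to treat analyses patients by allocated level, whatever they received. For efficacy in a randomised trial that is usually the cautious choice. For tolerability of repeated dosing it is not, because absence of a DLT in someone who was not dosed says nothing about the dose.

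Partial exposure is plausible here. RDT fractions are a subset of the 20 adjuvant RT fractions (in cohort 1, of the neoadjuvant ones). A cohort 8 patient could therefore miss some 5-ALA doses, complete 36 Gy and attend every follow-up visit. Nothing in the article says that such a patient has dropped out or would be replaced. Laboratory checks precede each 5-ALA dose ("Blood samples will be drawn for safety clearance as part of toxicity assessment"), and the Discussion accepts that cumulative liver toxicity or photosensitivity cannot be excluded.

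Levels hold only three to six patients, so one misclassified patient can change an escalation decision. The error runs in the unsafe direction.

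**Working it through.** **Inputs.** From the article: 3 + 3 patients per level, a level fails at two or more DLTs, 26 patients plus 15-20% drop-outs, and replacement at the same level. Assumed, because the article gives neither: the true DLT risk p at a level (0.20 to 0.50) and the share q of counted slots that are unexposed, DLT-free and not replaced. The 15-20% drop-out figure is borrowed as an anchor for q.

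**The plan's own figure.** 26 × 1.15 = 29.9 and 26 × 1.20 = 31.2; dividing instead, 26/0.85 = 30.6 and 26/0.80 = 32.5. The stated total of about 30 is reproduced at the lower drop-out figure, and the higher one gives slightly more.

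**Step 1: chance of passing a level.** A level passes with 0 DLTs in 3, or with 1 in 3 followed by 0 in the next 3:

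P(pass) = (1-p)³ + 3p(1-p)² × (1-p)³.

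At p = 0.33: 0.67³ + 3 × 0.33 × 0.67⁵ = 0.301 + 0.134 = 0.434.

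**Step 2: unexposed patients keep a slot.** If they carry no risk, p becomes p(1-q). At p = 0.33 this is 0.2805 for q = 15% and 0.264 for q = 20%.

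| True p | q = 0 | q = 15% | q = 20% |
|---|---|---|---|
| 0.20 | 0.709 | 0.773 | 0.793 |
| 0.25 | 0.600 | 0.681 | 0.709 |
| 0.33 | 0.434 | 0.535 | 0.570 |
| 0.40 | 0.309 | 0.415 | 0.454 |
| 0.50 | 0.172 | 0.270 | 0.309 |

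At p = 0.33 the rise is 10 to 14 points. If missed fractions only halve the risk, p becomes p(1-q/2), and P(pass) is 0.484 to 0.500, a rise of 5 to 7 points. Over a wider range of q with no risk in the unexposed, P(pass) is 0.467 at q = 5% and 0.641 at q = 30%.

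**Step 3: how often a slot is affected.** The chance that at least one of three slots is unexposed is 1 - 0.85³ = 0.386 at 15% and 1 - 0.80³ = 0.488 at 20%.

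**Step 4: drop-outs who are replaced.** A DLT-free drop-out adds nothing to a count of DLTs, and the replacement fills the slot, so P(pass) stays at 0.434. If a replaced drop-out's own DLT is counted, the rule becomes stricter. With one such patient in the first stage, whose own risk is r,

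P(pass) = (1-r) × 0.434 + r × 0.67⁶.

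This gives 0.378 at r = 0.165 and 0.321 at r = 0.33. The MTD count is therefore not biased upward by replaced patients.

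**Step 5: the DLT rate.** Replaced patients remain in an intention-to-treat denominator. As crude proportions, 2/6 = 0.333 becomes 2/7 = 0.286 with one and 2/8 = 0.250 with two. TITE-CRM does not by itself repair this. In its usual form it weights by follow-up time, so a patient entered at eight fractions who received three and completed follow-up carries full weight as a non-DLT at eight.

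**The case against.** The strongest objection is that the article never says under-dosed patients are scored as having tolerated their level. That follows from the intention-to-treat label, and a condensed article may leave the DLT definition and evaluability rules to the full protocol. The absence of those details is indeed no finding. But the article does state an analysis set for the primary endpoint, and reserves the dose-received set for other endpoints. That stated choice is the point.

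Second, drop-outs are replaced and the MTD is a count. A reader might infer that intention to treat biases the MTD upward through every patient who leaves. Step 4 shows that it does not. The MTD bias is confined to patients who miss fractions and keep their slot; replaced patients affect only the rate.

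Third, a much larger effect is tempting. If a quarter or a half of would-be DLT patients stopped first without a DLT, P(pass) at p = 0.33 would be 0.605 or 0.783. The arithmetic is right, but nothing in the documents supports such shares. Nor does drawing safety bloods amount to forecasting withheld doses.

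Fourth, patients are hospitalised with daily adverse-event monitoring, and the DSMB approves each next level after a six-week follow-up. This makes an unnoticed error less likely. It does not change the set in which the MTD and DLT rate are to be evaluated.

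**Conclusion.** The concern holds in a limited form. Intention to treat is the wrong stated set for an MTD defined by the number of RDT fractions. Its effect on the MTD is conditional: it is upward for patients who miss fractions without a DLT and are not replaced, and absent for DLT-free drop-outs who are. The final DLT rate is diluted by both groups.

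The illustrative size, 0.43 rising to 0.54-0.57 (or 0.48-0.50 with halved risk), rests on an assumed true risk of 33%, on 15-20% of slots being unexposed and not replaced, and on missed exposure being unrelated to susceptibility. The 15-20% is the article's figure for drop-outs, who are replaced, so the share that actually keeps a slot is unknown and may be smaller. The direction does not depend on these values; the size does.

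**What to change.** Change the analysis wording in three places.

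1. **Set for the primary endpoint.** Evaluate the MTD and DLT rate in a DLT-evaluable set: any patient with a DLT after a first RDT dose, or with all RDT fractions of the level given and the six-week follow-up completed.
2. **Replacement.** Define drop-out in Study population so that it matches this set, and any patient not evaluable for DLT is replaced at the same level.
3. **Other analyses.** Keep intention to treat for OS, PFS and EFS, and report the intention-to-treat DLT rate as a sensitivity analysis.

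An analysis by fractions received should only be supportive, and must allow for schedule. In Table 2 the first three RDT fractions of cohort 8 fall on days 1, 4 and 6, while those of cohort 3 fall on days 1, 6 and 11. Cohorts 0 and 1 each have one fraction, one adjuvant and the other neoadjuvant. Fraction count alone would pool these.

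The cost is about a paragraph of text and no new data, since the per-protocol definition already requires 5-ALA administration records. Some under-exposed patients would need replacement. The evaluable-set rate is also slightly conservative, because early stoppers without a DLT leave the denominator while DLTs stay. For example, assume a 5% DLT hazard per fraction and a 5% chance before each fraction of stopping. The true risk at eight fractions is 1 - 0.95⁸ = 34%. DLTs are observed in 0.0475 × (1 - 0.9025⁸)/0.0975 = 27% of all patients, and 0.9025⁸ = 44% complete without one. The evaluable-set rate is then 0.273/(0.273 + 0.440) = 38%, which errs on the safe side.

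### Tissue change is a secondary endpoint analysed by intention to treat, although its question is about the preoperative treatment the tissue actually received

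*Protocol article*

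**What the plan says.** Four places in the protocol article bear on the point.

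- **End-points.** The secondary endpoints are the six-month survival rates, "as well as histological tissue changes after neoadjuvant treatment". Tissue change is therefore secondary, not exploratory.
- **Statistical analysis.** The plan is "intention-to-treat”-evaluation for all cohorts’ primary and secondary endpoints". Exploratory endpoints are instead to be evaluated on a per-protocol basis, a term that "is defined as administration of RT- and 5-ALA-applications according to prescribed dose". The tissue endpoint is not exempted from the rule for secondary endpoints.
- **Blood and tissue samples.** The tissue analysis is described by treatment, with the cohort in brackets: "tissue changes after sole RT (cohort 0) as well as RDT (cohort 1").
- **Trial design, setting and recruitment, and Table 2.** Cohorts 0 and 1 both receive two neoadjuvant fractions, on days -3 and -2. They differ in that "in case of cohort 1, the first fraction will be conducted as RDT". Patients are allocated consecutively, three per cohort, with three more after a dose-limiting toxicity.

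**The concern.** Intention to treat earns its place by preserving a randomised comparison when patients depart from their assigned treatment. Here the cohorts are filled one after the other in a single-arm trial, so there is no randomised comparison to preserve. The tissue endpoint asks a mechanistic question: what irradiation does to the tissue with and without prior 5-ALA. The answer depends on what was given before resection, not on the cohort in which the patient was enrolled.

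The two labels agree as long as everyone follows the preoperative schedule. They separate when a cohort-1 patient is irradiated and resected without the day -3 dose. An analysis by cohort then reports sole-RT tissue under RDT. Only cohorts 0 and 1 supply this endpoint, so a single patient carries a lot of weight. The article also puts some weight on the early cohorts: the Discussion presents neoadjuvant treatment there as an extra safeguard for detecting excessive reactions in brain tissue.

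**Working it through.** The plan states no figure on this point, so there is none to reproduce. The check is a reading of the sections together, followed by an illustration of size.

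**1. Which rule applies.** End-points makes tissue change secondary. Statistical analysis gives secondary endpoints intention to treat and keeps per protocol for explorative ones. The article does not define intention to treat, so I take the usual meaning: analysis by allocated cohort.

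**2. What separates the cohorts before resection.** Both have fractions of 1.8 Gy on days -3 and -2. The section on drug administration also gives 5-ALA before anaesthesia, but to patients generally, so that dose does not distinguish the cohorts. The day -3 dose in cohort 1 is the only planned difference.

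**3. Where the cohort label and the treatment received part.**

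| Resected patient | Label by cohort | Preoperative treatment received |
|---|---|---|
| Cohort 1, schedule followed | RDT | RDT: labels agree |
| Cohort 1, both fractions, no day -3 5-ALA | RDT | sole RT: labels differ |
| Cohort 1, day -3 RDT given, day -2 fraction missed | RDT | RDT at 1.8 Gy instead of 3.6 Gy: label stands, dose deviation to be listed |
| Cohort 0, schedule followed | sole RT | sole RT: labels agree |
| Cohort 0, no neoadjuvant fraction given | sole RT | no preoperative RT: labels differ |

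A patient who is not resected supplies no tissue and does not enter the question. The second row is the main case.

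**4. Weight of one such patient.** The share of the nominal RDT group is 1/n: 1/3 = 33% with n = 3 and 1/6 = 17% with n = 6. If that patient's tissue behaves like sole-RT tissue, any mean difference between the two groups is expected to shrink to (n - 1)/n of its true size: 2/3 = 67% or 5/6 = 83%.

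**5. How likely it is.** The documents give no rate, so the following rests on assumed probabilities q that a resected cohort-1 patient missed the dose, taken as independent between patients. The chance of at least one is 1 - (1 - q)^n.

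| Assumed q | n = 3 | n = 6 |
|---|---|---|
| 5% | 1 - 0.95^3 = 14% | 1 - 0.95^6 = 27% |
| 10% | 1 - 0.90^3 = 27% | 1 - 0.90^6 = 47% |
| 20% | 1 - 0.80^3 = 49% | 1 - 0.80^6 = 74% |

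The 15–20% drop-out allowance under Study population is not an estimate of q. It concerns drop-outs over the whole study, not missed preoperative doses in patients who go on to resection.

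**The case against.** The strongest reply is that the article does not contradict itself. It ties each exposure to a cohort, and Table 2 gives those cohorts exactly those exposures, so a mismatch needs a deviation. The deviation is narrow: one oral dose missed on day -3 by a patient who is then irradiated and resected. Patients are hospitalised for the treatment course, so this may be rare. The wording that analyses will include intention to treat leaves room for a further analysis by treatment received, and detailed analysis sets are often left to a fuller document. All of this stands, and it limits the importance of the point. It does not remove it, because the article does not leave the choice open: it names a principle for this endpoint, and the principle does not suit it.

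Several stronger readings are tempting, and the documents do not support them.

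- *That the plan says untreated cohort-1 tissue counts as RDT tissue.* It does not say so. This follows from the usual meaning of an undefined term.
- *That a true 5-ALA effect would be missed.* No test or estimate of cohort 1 against cohort 0 is specified for tissue. The article promises descriptive measures and comparison with historical data, so the shrinkage in the working is an illustration, not the failure of a planned test.
- *That any missed neoadjuvant fraction mislabels the tissue.* Only the day -3 fraction is RDT in cohort 1. Missing only the day -2 fraction leaves the RDT label correct.
- *That per-protocol rules would discard good tissue because of later adjuvant events.* This needs tissue change to be exploratory. The Abstract mentions tissue effects apart from the named secondary endpoints, but End-points lists them as secondary, and that explicit list governs. The per-protocol definition is not applied to tissue. For the same reason, the exploratory marker samples taken around the neoadjuvant fractions are not part of this point.

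**Conclusion.** The point holds in a limited form. As written, the plan would analyse tissue change by allocated cohort, while the question it is meant to answer is about preoperative treatment received. The two differ only if a resected patient departs from the preoperative schedule. If one cohort-1 patient did not receive the day -3 dose, one third of the nominal RDT group (one sixth after expansion) would be sole-RT tissue.

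The conclusion rests on the usual meaning of intention to treat and on the absence of any stated exception for tissue. The probabilities in the working rest on assumed rates and carry no evidence about this trial. The endpoint is largely descriptive in three to six patients per cohort. Neither the maximum tolerated dose nor the six-month survival, progression-free and event-free rates are affected. It is worth changing because the better rule is clear and costs almost nothing.

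**What to change.** Add one sentence to Statistical analysis: histological tissue change in cohorts 0 and 1 is analysed by the preoperative RT and 5-ALA actually received, whatever happens during adjuvant treatment, with the by-cohort result shown beside it.

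List every preoperative deviation by patient. Include a missed day -2 fraction, and state that it does not by itself remove the RDT label. Report tissue from a cohort-1 patient irradiated without the day -3 dose with the sole-RT tissue and mark it as such.

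The cost is a wording change, with no change to treatment, visits or samples. The downside is that the RDT tissue group may be smaller than the cohort, which at this size should be stated openly.

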#### Drug administration

Oral 5-Aminolevulinic acid will be applied on RDT-treatment days as a solution in tap water with a dose of 20 mg/kg bodyweight between seven and nine hours prior to 1.8 Gy-irradiation. Additionally, patients will receive 5-ALA four hours prior to induction of anesthesia for surgery. Use of additional concomitant chemo- or immunotherapy is prohibited during trial participation.

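### Intention-to-treat analysis of the primary endpoint, with every drop-out replaced, keeps DLT-free patients who did not receive the assigned RDT fractions in the final DLT rate

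*Protocol article*

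**What the plan says.** All references are to the protocol article; no separate SAP is at hand.

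- Statistical analysis: intention-to-treat "evaluation for all cohorts’ primary and secondary endpoints", and per-protocol "evaluation for explorative endpoints" only. Per-protocol "is defined as administration of RT- and 5-ALA-applications according to prescribed dose". The same section has the final DLT rate estimated by TITE-CRM.
- End-points: the primary endpoint is the MTD and safety, and "MTD is defined as maximum dose level before two or more patients suffer from DLT".
- Trial design, setting and recruitment: "Each cohort encompasses three initial patients being expanded by additional three participants in case of a dose limiting toxicity (DLT), following a 3 + 3-design". Dose level means the number of RDT fractions. The next level is opened after six weeks of follow-up from the last RT fraction of a cohort's last patient.
- Study population: "26 patients will be recruited with additional 15–20% drop-outs, cumulating in approximately 30 patients". Also: "For each drop-out, a new patient will be entered into the study at the same dose level".

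**The concern.** A DLT rate at a dose level describes what happens to patients who were given that dose, or who had a DLT while it was being given. In a single-arm escalation trial there is no randomised comparison for intention to treat to protect, so its usual justification is absent. The article does define a set by what was actually administered, but it assigns that set to the exploratory endpoints and gives the toxicity endpoint the set that ignores exposure.

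The schedule in Table 2 shows how the two can part:

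- In cohort 8, RDT falls on days 1, 4, 6, 9, 11, 14, 16 and 19. A patient who stops after day 5 has had two of eight fractions, yet counts as DLT-free at eight.
- In cohort 0 the only RDT fraction comes on day 1 of adjuvant RT, two to six weeks after surgery. A patient lost in that interval has had no RDT fraction at all.

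Because each drop-out is also replaced, the escalation decision would in practice rest on the refilled cohort while the reported rate rests on everyone. That gives two denominators for one endpoint. At stake is a reported DLT rate that looks safer than it is, in a trial whose Discussion names cumulative effects of repeated dosing as an open safety question.

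**Working it through.** **Inputs.** 26 patients plus 15–20% (Study population); three patients per level, expanded to six after a DLT (Trial design); two or more DLTs at a level (End-points); TITE-CRM for the final rate (Statistical analysis). Assumption: intention to treat has its usual meaning, that is, everyone allocated to a cohort is counted there.

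**1. The plan's own total.** 26 × 1.15 = 29.9 and 26 × 1.20 = 31.2. The stated figure of about 30 is reproduced at the lower end of the range.

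**2. One dose level.** Let x be the DLTs among n exposed patients and k the DLT-free drop-outs kept by intention to treat. The rate moves from x/n to x/(n + k).

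| Exposed patients | k = 1 | k = 2 |
|---|---|---|
| 1/6 = 16.7% | 1/7 = 14.3% | 1/8 = 12.5% |
| 2/6 = 33.3% | 2/7 = 28.6% | 2/8 = 25.0% |

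**3. Whole trial, average.** If all planned drop-outs are DLT-free and fully weighted, the rate is multiplied by 26/[26 × (1 + d)] = 1/(1 + d).

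- d = 15%: 1/1.15 = 0.87
- d = 20%: 1/1.20 = 0.83
- With the rounded total: 26/30 = 0.87

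An illustrative true rate of 30% would read 0.30 × 0.87 = 26% to 0.30 × 0.83 = 25%.

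**4. Does TITE-CRM remove it?** The article gives no model settings, so this is an illustration at one level: power model p = 0.25^exp(b), with b normal, mean 0 and variance 1.34 (assumed). Likelihood for 2 DLTs in 6 exposed patients plus one DLT-free drop-out with follow-up weight w: p² × (1 − p)⁴ × (1 − w·p).

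| Weight w of the drop-out | Posterior mean DLT rate |
|---|---|
| 0 (same as no drop-out) | 0.349 |
| 0.25 | 0.342 |
| 0.5 | 0.333 |
| 1.0 | 0.309 |

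The shift is 0.7 to 4.0 percentage points. It vanishes only at w = 0. The weight depends on time observed: a patient who stops RDT early but is watched to the end of the window gets w = 1, whatever number of fractions was given.

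**5. Does it reach the MTD?** The rule counts DLTs. 2/6, 2/7 and 2/8 all contain two DLTs and lead to the same decision. What could hurt the rule is an unexposed patient filling one of the first three places. With p = 0.30, the probability of escalating is:

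- three exposed patients: 0.7³ + 3 × 0.3 × 0.7² × 0.7³ = 0.494
- two exposed patients, not replaced: 0.7² + 2 × 0.3 × 0.7 × 0.7³ = 0.634

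Replacement prevents the second case.

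**The case against.** The strongest reply is that the article condenses a longer protocol, which may define drop-out, a replacement window and an evaluable set. That stands for the definitions. It does not answer the main point, because the article does not leave the analysis set for the primary endpoint open: it names intention to treat. A second fair reply is that the numbers are small and TITE-CRM softens them. That also stands, within the limits shown above.

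Several stronger readings are tempting, and the article does not support them.

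- *The MTD is diluted too.* It is a count rule, and replacement restores the exposed patients.
- *Patients who leave because of toxicity are lost.* Under intention to treat a patient who leaves with a DLT stays counted. The replacement then adds a further chance of reaching two DLTs.
- *Overall survival loses patients who progress and start other treatment.* The Drug administration section says "Use of additional concomitant chemo- or immunotherapy is prohibited during trial participation", but nothing states that such a patient becomes a drop-out or that survival follow-up ends. Intention to treat for secondary endpoints would keep that patient.
- *A late leaver sends a new patient to a level already cleared.* This rests on reading one condensed sentence literally, with drop-out undefined. The full protocol may limit it.
- *The factor is 0.80–0.85.* That takes 15–20% as a share of all enrolled patients; the article adds it to 26.

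**Conclusion.** The point holds for the final DLT rate and not for the MTD. As written, the plan keeps in the denominator DLT-free patients who did not receive the assigned RDT fractions, and the bias runs towards safety. One such patient at a level of six lowers the crude rate by about 2 points (from 1/6) to 5 points (from 2/6). Over the whole trial, 0.83–0.87 is the worst case.

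That worst case assumes that every planned drop-out is DLT-free, has full weight and was not meaningfully exposed. Drop-outs with short follow-up, or who had received most of their fractions, would cause less. The article does not say when or why patients are expected to leave, so the actual size cannot be fixed. The direction can.

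**What to change.** In Statistical analysis, replace intention to treat for the DLT rate with a DLT-evaluable set made up of:

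- patients with a DLT at any time after first RDT exposure;
- patients who received all assigned RDT fractions and completed the six-week follow-up;
- patients who stopped RDT because of toxicity, even if it fell short of a DLT, so that intolerance is not removed from the rate.

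State that patients replaced for reasons unrelated to toxicity leave this denominator, and use the same set for escalation decisions and the final rate. Listing the fractions received by each patient would show who in the third group was only partly exposed. Keep all treated patients for adverse events, and intention to treat for survival as the section already has it.

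The cost is a few sentences and no extra patients or data. The reported DLT rate may look slightly less favourable.
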